## Abstract

**Background:**

Indigenous Australian youth (aged 15 to 34) have up to four times the risk of suicide compared with their non-Indigenous counterparts. Barriers to help-seeking include shame, feared loss of autonomy and negative attitudes towards healthcare providers. The use of mobile devices and apps continues to rise amongst young people, thus presenting opportunities to utilize these aids in overcoming help-seeking barriers. Apps have been shown to assist in several health-related areas, including weight loss and smoking cessation, although no apps have as yet been evaluated for suicide prevention. Moreover, there is a lack of research that scientifically evaluates suicide prevention interventions within Indigenous communities.

**Methods/Design:**

In this study, a recently developed self-help app will be evaluated in a randomized controlled trial. The intervention is based on acceptance and commitment therapy and mindfulness-based cognitive behavioural therapy. It is aimed at participants who have suicidal thoughts but who are not actively suicidal. In total, 150 participants will be randomly allocated to the intervention-condition (*N* = 75) or to the wait-list control condition (*N* = 75). Questionnaires will be completed at baseline, post-test and 6 weeks follow-up. The primary outcome measure is a reduction in frequency and intensity of suicidal thoughts. Secondary outcome measures are the reduction of depression, anxiety and impulsivity.

**Discussion:**

This study is the first to evaluate the effectiveness of a self-help app for suicidal thoughts amongst young Indigenous people. Several limitations and strengths of the design are discussed.

**Trial registration:**

Australian New Zealand Clinical Trials Registry (ANZCTR): ACTRN12613000104752.

## Background

Suicide is the leading cause of death for Australians aged 15 to 34. The suicide rate for Indigenous people has increased dramatically over the past 30 years despite decreases in that for the general population. Overall, the suicide rate for Indigenous populations is twice that for non-Indigenous people with Indigenous youth being most at risk [1]. Compared with their non-Indigenous counterparts, Indigenous youth aged 15 to 24 have four times the risk of suicide, with those aged 25 to 34 having almost three times the risk [2].

Help-seeking amongst Indigenous populations is considerably lower than in the general community. Only 14% of Indigenous people who had a diagnosable mental illness at the time of suicide sought prior mental health treatment [3]. Lack of anonymity is problematic where individuals are part of a closely interwoven community and health workers are known to the help-seeking individual. Shame, stigma and the need to maintain esteem within the community are major barriers to help-seeking, as are cost (service or transport), service availability and service suitability [4].

Anonymous support may overcome some of these obstacles, and although the internet has gone some way to addressing help-seeking barriers in some communities, portable devices and apps may provide a more accessible means of support. The use of portable mobile devices (including smartphones and tablets) is increasing rapidly amongst youth. In mid-2012 more than 1.4 million apps were available on the market, some of which aimed to help people with their mental health and wellbeing or aid in the prevention of suicide. However, most have not been evaluated to determine their effectiveness.

Thirty-four per cent of people experiencing suicidal ideation go on to make a plan, and 29% attempt suicide [5]. This suggests that suicide prevention efforts need to be aimed at those with suicidal ideation. There is evidence that cognitive behavioural therapy, dialectical behaviour therapy and other cognitive interventions (that is, schema focused and problem solving therapies) are effective in reducing self-harm and suicidal behaviours [6,7]. Mindfulness-based cognitive therapy has also shown promising results in reducing suicidal ideation [8].

The current intervention uses acceptance and commitment therapy, the ‘third wave’ of cognitive behavioural therapy [9]. Although acceptance and commitment therapy is rigorously behavioural and based on scientific validity of human cognition, it also addresses issues of spirituality, values and self, components that have been identified as crucial to successful indigenous suicide prevention strategies. The goal of acceptance and commitment therapy is to assist individuals to cease struggling against their internal experiences, such as thoughts, feelings, memories and sensations, and help them move in valued directions by implementing effective behavioural changes. Acceptance and commitment therapy has been found to be efficacious in a number of mental health domains, including depression [10], anxiety [11] and stress [12]. It has demonstrated effect sizes similar to that of traditional cognitive behavioural therapy and superior effects to control conditions for a range of mental and physical health disorders [13].

Emerging evidence suggests that online intervention to prevent suicide is feasible and effective [14,15]. An international systematic review of suicide prevention for Indigenous populations identified only three studies based in Australia, none of which were controlled trials [16]. Given the prevalence of suicide amongst this community, there is an urgent need for feasible, acceptable interventions with evidence of effectiveness.

This pilot study has several aims including: assessing whether the app can reduce suicidal thinking, psychological distress or impulsivity; evaluating the acceptability of the app to young Indigenous people; assessing the feasibility of the recruitment, screening and randomization methods; examining uptake and adherence to the app; and evaluating the safety, security and clinical support protocols.

## Methods/Design

### Design

This study is a randomized controlled trial comparing a self-help app intervention with a wait-list control condition. The intervention is aimed at persons with suicidal thoughts but without active suicidal intent. Participants in the control condition will have access to the intervention after the experimental group has finished (that is, after six weeks). Assessments will take place at baseline, immediately after intervention completion, and 6 weeks follow-up. This study was approved by the University of New South Wales Human Research Ethics Committee (protocol no. HC13025) the Western Australian Aboriginal Health Ethics Committee (protocol no. 486), and the Kimberley Aboriginal Health Planning Forum (protocol no. 2013–006).

### Sample size

A maximum of 150 participants will be recruited for the study. Power analysis for the primary outcome measure indicates that 98 participants are needed for a medium effect size. We anticipate that some participants will be lost to follow-up, lose their tablets or incur damage to them, thus the data that we obtain at the end of the trial is likely to come from fewer than the 150 registered participants.

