### Statistical analyses

To test the hypothesis that the self-help intervention is superior to the control condition, the analysis will be conducted on an intention-to-treat basis following the pertinent BMJ & Consort guidelines. Missing observations at follow-up will be imputed by regression imputation or multiple imputations, stratified for predictors of outcome and loss to follow-up. Relative improvements in frequency and intensity of suicidal thoughts for the experimental group in comparison with the control group will be calculated using Cohen’s *d*. For this confirmatory analysis the primary outcome measure is used (the DSI-SS). For the analyses of the secondary outcome measures, a Bonferroni correction will be applied to control the overall Type I error rate.

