## Discussion

This paper describes the study protocol for a pilot randomized controlled trial of an app for suicide prevention in young Indigenous people. To our knowledge, this is the first trial of a mobile-based app for suicide prevention, and the first randomized controlled trial of suicide prevention with Indigenous Australians. Despite fears that focusing on suicidal ideation might give rise to further suicidal thoughts and even attempts, there is no evidence to validate this idea [15,28].

Several limitations apply to the study protocol of this self-help app. First, online interventions tend to have a high attrition rate. Dropout from the study can introduce a selection bias and therefore be a threat to validity. To minimize this, participants will be asked for additional contact details so that even if the intervention is not completed, follow-up assessments may still be collected. Further, each participant will be contacted via email or text message three weeks into the intervention or wait-list period for a brief assessment. A reminder to continue with the app will be provided at this point.

A further limitation is that none of the measures provides a psychiatric diagnosis. The intent is to keep the measures to a minimum in order to increase retention, as the research participants may find too many measures a barrier to participation. Some participants are also likely to have low literacy skills. Long, complex measures would be a significant problem for these participants. To overcome literacy problems, participants have the option of face-to-face or telephone assistance to complete the measures. Moreover, the app targets suicidal ideation irrespective of diagnosis and, as such, a measure of suicidality is a more appropriate primary outcome measure.

Researching suicide prevention is difficult; perhaps even more so within Indigenous communities. Because of this, little is known about what works with this population. While suicide rates have dropped amongst the general population over the last two decades, they remain stubbornly high in the Indigenous community [29]. This study will make a significant and unique contribution to our knowledge about suicide prevention and treating suicidal ideation.

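### The stated need for 98 participants is supported, on a two-sided test, only if baseline information is used, and the described comparison names no baseline adjustment

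*Protocol article*

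**What the plan says.** The Sample size section sets a ceiling of 150 recruits and states: "Power analysis for the primary outcome measure indicates that 98 participants are needed for a medium effect size". It expects some loss but gives no rate. It does not give a numeric effect size, alpha, sidedness, power, test or baseline correlation.

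The Statistical analyses section states a superiority hypothesis: "To test the hypothesis that the self-help intervention is superior to the control condition". It then says "Relative improvements in frequency and intensity of suicidal thoughts for the experimental group in comparison with the control group will be calculated" as Cohen's d, and adds "For this confirmatory analysis the primary outcome measure is used (the DSI-SS"). No test or model is named. The text says neither that the comparison is adjusted for baseline nor that it is not. A Type I error correction is mentioned for the secondary outcomes only, without a level.

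Under Design: "Assessments will take place at baseline, immediately after intervention completion, and 6 weeks follow-up". Table 1 confirms that the DSI-SS is collected at all three times. The Abstract gives 75 participants per arm. On attrition, the Discussion notes that "online interventions tend to have a high attrition rate".

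**The concern.** A medium standardised difference is conventionally d = 0.5, and the textbook two-sided comparison of two means at 80% power needs about 128 participants in total. The stated 98 is 30 fewer. The analysis section names nothing, such as a baseline covariate, that would close the gap.

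The number matters because it is the reference point for attrition. Set against 150 recruits, a need of 98 suggests room for roughly a third to be lost, in a trial that expects substantial dropout. If the analysis then turns out to be a plain comparison, a null result on suicidal ideation from about 98 completers could be taken as adequately powered when it is not.

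**Working it through.** **Inputs from the article.** Total needed 98; ceiling 150; 1:1 allocation (75 + 75); outcome DSI-SS; DSI-SS measured at baseline, post-test and follow-up.

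**Inputs assumed, because the article gives none.** Medium effect d = 0.5 (equivalently f = 0.25), alpha 5%, power 80%. Both one- and two-sided tests were tried. The baseline correlation r was varied. N is the total, in equal arms.

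**1. Which calculations reproduce 98?**

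- *ANCOVA of post-test on arm and baseline, two-sided.* Baseline adjustment multiplies the variance by (1 − r²), so the noncentrality is λ = d²N / [4(1 − r²)] with 1 and N − 3 degrees of freedom. At r = 0.5 and N = 98, λ = 0.25 × 98 / (4 × 0.75) = 8.17 and power is 0.808. At N = 96, λ = 8.00 and power is 0.799. So 98 is the smallest even total that reaches 80%.
- *Repeated-measures group main effect, two occasions, r = 0.5.* λ = f²Nm / [1 + (m − 1)r] = 0.0625 × 98 × 2 / 1.5 = 8.17, with power 0.808 at 98 and 0.799 at 96. This also gives exactly 98. However, the test averages baseline with post-test. Randomised arms should not differ at baseline, so this is not a test of the treatment effect.
- *Change score, two-sided.* The variance is multiplied by 2(1 − r), so the effective difference is 0.5 / √[2(1 − r)]. At r = 0.62 this is 0.5 / √0.76 = 0.574, and the total is 98.
- *One-sided test of two means.* The normal approximation gives N = 4 × [(1.645 + 0.842) / 0.5]² = 98.9 before rounding, or 100 in equal arms. The exact t calculation gives 102. Power at 98 is 79.2% (exact) or 79.7% (normal).

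**2. What does a two-sided comparison without baseline adjustment need?**

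The noncentrality is δ = d√(N/4) with N − 2 degrees of freedom.

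| N | δ | Two-sided power |
|---|---|---|
| 98 | 2.47 | 68.8% |
| 128 | 2.83 | 80.1% |
| 150 | 3.06 | 86.0% |

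The normal approximation gives 4 × [(1.960 + 0.842) / 0.5]² = 125.6, or 126 in equal arms. With 98 participants, 80% power requires d = 0.57.

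**3. How sensitive is the need to the baseline correlation?** (two-sided, 80% power)

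| r | ANCOVA total | Change-score total |
|---|---|---|
| 0.3 | 118 | – |
| 0.4 | 108 | 154 |
| 0.5 | 98 | 128 |
| 0.6 | 84 | 104 |

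At r = 0.5 the change-score variance factor is 2(1 − 0.5) = 1, so a comparison of improvements gains nothing over a comparison of post-test means.

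**4. Loss from 150 that each figure allows.** 1 − 98/150 = 34.7%; 1 − 128/150 = 14.7%.

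**The case against.** The strongest reply is that the article does not say the comparison is unadjusted. It names an outcome (improvement) and an effect-size metric. Cohen's d can be reported beside an ANCOVA, a change-score test or a repeated-measures model. Improvement implies reference to baseline, and the DSI-SS is collected there. An ordinary two-sided ANCOVA with r = 0.5 returns exactly 98. The hypothesis is also directional, and a one-sided test at 98 falls less than one percentage point short of an assumed 80%. Finally, a journal article commonly leaves alpha, power and the model to the full protocol or SAP, and this trial is called a pilot with several feasibility aims.

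Most of this stands. A reader might infer that 98 is a miscalculation, or that it is refuted on both the two-sided and the one-sided reading. The documents support neither inference. The settings behind 128 and 69% are conventions, not inputs stated in the article, and the one-sided route cannot be excluded. The missing inputs alone would not be a finding. Nor does the article claim that a third of participants may be lost; that follows only from dividing 98 by 150.

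What does not stand is that the word improvement settles the matter. A change score with r = 0.5 still needs 128 and reaches 98 only near r = 0.62. The article commits to a number and describes a comparison, and on a two-sided test the two agree only through an adjustment or a correlation that it does not name. The pilot label does not remove this, because the DSI-SS analysis is called confirmatory.

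**Conclusion.** The concern holds in a limited form. The figure of 98 is not shown to be an arithmetic error, but on a two-sided test the comparison described does not support it unless baseline information is used. Under d = 0.5, two-sided 5% and 80% power, all assumed, the need without adjustment is about 128 and power at 98 is about 69%. With ANCOVA, 98 is right at r = 0.5, more than enough at 0.6 (84 needed), and too few at 0.4 (108) or 0.3 (118). The article gives no correlation, so which case applies cannot be settled from it.

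Severity is moderate. Recruitment of 150 gives 86% power without any adjustment if nobody is lost, so what is at stake is how much attrition the trial can absorb and how a null result is read.

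**What to change.** Keep recruitment at 150 and tie the number to a test, in one of two ways:

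- **Preferred.** Make the primary test a two-sided 5% ANCOVA of post-test DSI-SS on arm and baseline DSI-SS. State that 98 assumes d = 0.5, 80% power and a baseline correlation of at least 0.5. Cohen's d can still be reported as the effect size.
- **If no adjustment is intended.** Restate the need as 128 analysable participants (64 per arm), and note that this allows about 15% loss from 150 rather than 35%.

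A one-sided test should not be adopted simply to arrive at 98.

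The cost is wording only. Baseline DSI-SS is already collected and no extra recruitment is needed. The second option makes the allowance for attrition visibly tighter.

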### Eligibility criteria and screening

Eligibility to take part in the pilot is determined in a stepwise screening process. To be eligible, participants must be: aged 18 to 30; able to attend two or three face-to-face sessions in Armidale, Sydney or Broome; consent to be asked questions of a personal nature; not have been diagnosed with a psychotic disorder such as schizophrenia; have had suicidal thoughts in the past two weeks; not be severely suicidal; and be willing to make contact with the Suicide Call Back Service.

Participants who meet the inclusion criteria will be administered the Kessler Psychological Distress Scale (K10) [17] and Patient Health Questionnaire-9 (PHQ-9) [18]. Participants are excluded from the study if they answer, ‘Not at all’, to item 9 on the PHQ-9, which asks participants to categorize how frequently they have had ‘Thoughts that you would be better off dead or of hurting yourself in some way’, over the previous fortnight.

Individuals are then asked several suicide intent questions. Those who indicate immediate intent to take their life and have a plan to do so are excluded from the study and receive Applied Suicide Intervention Skills Training. If their intent to suicide is reduced at the end of this intervention, they are given referral information to the Suicide Call Back Service. Alternatively, if the participant still expresses intent to suicide, their local acute care team will be called, and their contact details will also be given to a clinical psychologist for follow-up within 72 hours. Eligible participants who have indicated distress (by scoring >19 on the PHQ-9 or >29 on the K10) will still be admitted to the study, but will be referred to support services.

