### Inclusion procedure

Participants will be screened over the phone and those eligible will be given a time for their induction session. Participants in remote locations may opt to have the tablet couriered and to have their induction over the telephone. During induction, participants will read a participant information statement, sign a consent form and safety agreement, be administered baseline measures and complete a follow-up contact form so that the researchers can make contact with them or their closest contact for post-test and follow-up measures. Individuals in the intervention group will be provided with a tablet and basic training on how to use the app, as well as assistance in setting up their security access. Those in the wait-list control group will be asked to return to the same location after 7 weeks, at which point they will be given a tablet and basic app training. An overview of the process is given in Figure 1.

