### Screening

#### Recruitment

Recruitment will take place via the Black Dog Institute (on its website and through their volunteer research registry), through advertisements on social networking sites, and through partner organizations *Alive and Kicking Goals!* in Broome and *BackTrack* in Armidale.

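### The eligibility list does not match the stated population: it omits Indigenous status, conflicts with telephone induction, and leaves the suicidal-intent rule unclear

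*Protocol article*

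**What the plan says.** **Population.** The Discussion part of the Abstract states: "This study is the first to evaluate the effectiveness of a self-help app for suicidal thoughts amongst young Indigenous people". The main Discussion says: "This paper describes the study protocol for a pilot randomized controlled trial of an app for suicide prevention in young Indigenous people", and claims "the first randomized controlled trial of suicide prevention with Indigenous Australians". The aims at the end of Background include acceptability to young Indigenous people.

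**Eligibility.** The list under Eligibility criteria and screening begins: "To be eligible, participants must be: aged 18 to 30; able to attend two or three face-to-face sessions in Armidale, Sydney or Broome". It then requires consent to personal questions, no diagnosed psychotic disorder, suicidal thoughts within the last two weeks, absence of severe suicidality, and willingness to contact the Suicide Call Back Service. Those who pass complete the K10 and PHQ-9, and a negative answer to PHQ-9 item 9 excludes. Suicide intent questions follow.

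**Recruitment.** Besides two partner organizations in Broome and Armidale, the trial recruits through social networking advertisements and through the coordinating institute, "on its website and through their volunteer research registry".

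**Attendance.** Under Inclusion procedure: "Participants in remote locations may opt to have the tablet couriered and to have their induction over the telephone".

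**Intent.** Design says: "The intervention is aimed at persons with suicidal thoughts but without active suicidal intent". The Methods part of the Abstract makes a similar statement. The rule at the intent step is: "Those who indicate immediate intent to take their life and have a plan to do so are excluded from the study".

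**The concern.** An eligibility list decides who is randomized and therefore to whom the result applies. This one leaves out the characteristic that defines the trial's population, and part of the recruitment comes from sources that are not specific to that population. If non-Indigenous people were enrolled, the estimated effect would belong to a mixed group, and the claim to be a first trial with Indigenous Australians would not be supported by the sample.

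The attendance criterion pulls the other way: it can bar remote people for whom the trial has arranged a way in.

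The intent wording bears on participant safety. If the general description and the screening rule draw the line in different places, two screeners could reach different decisions about the same person, who could then be allocated to either the app or the wait-list.

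**Working it through.** The plan gives no figure on this point, so the check sets the sections side by side and follows three hypothetical people through the stated steps.

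**(a) Indigenous status**
- Population claimed: young Indigenous people (Abstract, Background, Discussion).
- Criteria listed: age, attendance, consent, no psychotic disorder, recent suicidal thoughts, not severely suicidal, willingness to contact the call-back service. Indigenous status is absent.
- Could recruitment supply it? Not by itself. A website, a volunteer registry and social networking advertisements are not described as restricted to Indigenous people.
- Could another step supply it? Table 1 shows a first screener part consisting of questions whose content is not given. It also shows demographic questions, but at baseline, which is administered at induction to people already found eligible. Demographics could record Indigenous status but would not act as an entry condition.
- Trace: a non-Indigenous person aged between 18 and 30, living near one of the three places, recruited from the registry, with recent suicidal thoughts and no intent, meets every printed criterion.

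**(b) Attendance**
- Eligibility: the person must be able to attend two or three sessions in person at one of three named places.
- Inclusion procedure: a remote participant may receive the tablet by courier and be inducted by telephone.
- Trace: a remote person who cannot travel to any of the three places fails the first section, although the next section provides for remote entry.

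**(c) Intent**
- Design: the target group has no active intent. A plan is not mentioned.
- Intent step: exclusion is stated for immediate intent together with a plan.
- Eligibility list: severe suicidality is barred, but the term is not defined or linked to the five intent questions counted in Table 1.
- Order of steps: the severity criterion belongs to the inclusion list, and the questionnaires and intent questions come after it. At that later step the plan still expects to meet people with immediate intent and a plan. The printed sequence therefore does not show that the severity criterion has already removed people with intent alone.
- Trace: a person with immediate intent and no plan is outside the group described under Design, is not excluded by the intent step, and may or may not be excluded by the severity criterion. The text gives no answer.

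**The case against.** The strongest reply is that this is a condensed article. Its population is stated several times, two Aboriginal health bodies are among those that approved the study, screening is described as stepwise, and neither the first screener part nor the study-procedure figure can be seen. Indigenous status may well be asked there, and advertisements can be targeted. This stands as far as conduct is concerned. A reader might infer that the sample will be mixed, or that a non-Indigenous person who meets the list has to be enrolled. The documents support neither: meeting criteria does not oblige enrolment, and nothing shows that any such person will be recruited. Condensation does not explain the omission itself, however. The list is detailed enough to include consent to personal questions, yet it leaves out the defining trait.

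On intent, a reader might conclude that people with immediate intent but no plan are admitted. That goes too far. The bar on severe suicidality could exclude them, the intent questions are not printed, and the Abstract and Design say only whom the intervention is aimed at, which describes a target group and is not an entry rule. What remains is an undefined term and wording that does not agree.

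On attendance, telephone induction is optional and does not expressly waive the other sessions, and some remote people can travel. It does not follow that all remote participants are ineligible. The mismatch affects those who cannot travel.

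**Conclusion.** The concern holds in this form: the printed eligibility list does not define the population the trial says it studies.

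- The omission of Indigenous status is the most consequential part, because the main conclusion depends on it.
- The attendance conflict is real but minor.
- The intent wording is unresolved: it is unclear whether intent without a plan excludes. This review takes no position on which rule is right.

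No numerical size can be given. The documents state no expected non-Indigenous share, which could be zero, and no expected number of remote participants. A reader might try to express the problem as lost power in an Indigenous subgroup. That would rest on an invented share and on a subgroup analysis the article does not plan. The verdict assumes that the printed list is meant to be complete, as its wording suggests. If the unseen screener already asks about Indigenous status and makes it a condition, the first part reduces to a correction of the published text.

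**What to change.** 1. Add self-identification as Aboriginal and/or Torres Strait Islander to the list under Eligibility criteria and screening, and ask it in the first screener part. Recruitment is already under way, so confirm it for those already enrolled.
2. Align the attendance criterion with Inclusion procedure, so that it is clear which sessions a remote participant must attend in person and which may be done by telephone.
3. Have the clinical team reconcile the Abstract, Design and Eligibility criteria and screening into one intent rule, define the severity criterion, and map both to the five intent questions. The choice of rule is theirs.

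The cost is a short amendment, one screening question and a check of existing records. Recruitment through the general channels may be slower.
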